**Symptom variables**							
	Depression	Patient Health Questionnaire (PHQ-9)	Client	✓	✓	✓	✓
	Anxiety	Generalized Anxiety Disorders Scale (GAD-7)	Client	✓	✓	✓	✓
	Suicidal ideation	Columbia-Suicide Severity Rating Scale (CSSRS)	Clinician	✓	✓	✓	✓
**Functional variables**							
	Quality of life	World Health Organization-Five Well-Being Index (WHO-5)	Client	✓	✓	✓	✓

### Data Analysis

SPSS Version 26 (IBM Corp) will be used to analyze all quantitative data in accordance with the CONSORT guidelines [92]. Following an intention-to-treat approach, data will be analyzed with descriptive statistics, repeated measures, and correlational analyses. Descriptive data for baseline parameters will be presented using frequencies and percentages among the 2 intervention groups and compared using the chi-square test for categorical variables and the independent sample *t* test for continuous variables. The type of intervention (rTMS alone and rTMS plus Text4Support) will be considered the independent variable, while the scores of the various scales at each time point (6 weeks, and 3 and 6 months) will be considered the dependent variables for each of the analyses. Baseline scores of the respective scales will be used as covariates in the analyses.

To compare the effectiveness of the treatment interventions for the management of TRD among participants, the 1-way between-group analysis of covariance (ANCOVA) comparing changes in the mean scores from baseline to 6 weeks, and 3 and 6 months for all measures will be employed. Preliminary checks will be conducted to ensure there is no violation of the assumption of normality, linearity, homogeneity of variance, homogeneity of regression slopes, or reliable measurement of the variate before ANCOVA is conducted. For participants with missing data, the last observation will be imputed before performing sensitivity analyses of covariance to explore the impact of the imputation of data loss on the PHQ-9 and the secondary measures at each time point.

The chi-square test or Fisher exact test will be employed to compare the prevalence of depression symptoms using the PHQ-9, the prevalence of anxiety symptoms using the GAD-7, suicidal ideations using the CSSRS, and quality of life using the WHO-5 between the 2 intervention groups at all time points in the overall sample.

Furthermore, a paired *t* test will be used to examine the changes in the mean scores of the PHQ-9, GAD-7, CSSRS, and WHO-5 at baseline and 6 weeks for participants who complete the instruments at both time points. Frequencies and percentages will be used to report categorical variables, while mean scores, confidence intervals, and effect sizes will be used to report continuous variables. The 2-tailed α-level criterion for statistical significance will be set at *P*≤.05.

Qualitative data obtained through audio recordings from participant focus group discussion sessions will be transcribed and analyzed using thematic analysis aided by NVIVO software [93]. Data analysis will be both deductive and inductive. After familiarization with the transcripts obtained, 2 researchers will independently conduct the initial coding, and subsequently, the final coding criteria will be agreed by the 2 researchers. This will be followed by an iterative review of emerging themes as informed by the research questions. The final sets of themes and subthemes in relation to the overall study aims will be reported and supported with verbatim quotes.

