Data in the literature suggest that TRD is characterized by a disproportional socioeconomic burden for affected individuals, their relatives, and the health care system in general [19]. TRD presents with a higher direct and indirect medical cost than MDD, which is responsive to therapeutic interventions. This medical cost increases with the severity of TRD [20-23]. Compared with other depressive conditions, TRD leads to at least about 12% more outpatient attendance, is associated with about twice the chances of hospitalization, and is associated with the use of up to about 3 times more psychopharmacological medications [22]. Evidence in the literature suggests that the overall medical cost for hospitalization among patients with TRD is about 6 times greater compared to that among patients without TRD [22]. Similarly, the total cost of a TRD episode among patients with TRD is about 2.7 to 5.8 times higher compared to that among patients without TRD. This difference in cost is due to a longer duration of TRD episodes coupled with a greater rate of usage and a higher cost per treatment visit among patients with TRD [23]. Furthermore, the overall depression-related cost among patients with TRD is estimated to be about 19 times greater compared to that among patients with other depressive conditions [22]. Data suggest that up to about 47% of depression-related costs are attributed to TRD in the United States alone [21,24].

TRD is associated with several risk factors, which include physical or psychiatric conditions, such as anxiety disorders, personality disorders, and hypothyroidism; drug interactions; sociodemographic risk factors, such as individual education attainment and gender; and other external issues affecting ill health [21,25-27]. Furthermore, bipolarity is considered a major factor in TRD based on the inadequate management of bipolar diathesis in MDD, which is diagnosed as unipolar [26,28,29]. Again, TRD is characterized by a greater risk of comorbidities of both psychiatric and medical conditions, an increased risk of suicides, and impairment in normal functioning such as impaired quality of life and social functioning [20,30-32]. Due to its recurrent nature, an estimated 80% of patients with TRD relapse within 1 year after remission of their symptoms [30].

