#### Exclusion Criteria

The exclusion criteria are as follows: (1) Age less than 18 years; (2) Diagnosis (current unless otherwise stated) of a neurological disorder (including a history of seizures), a primary or secondary tumor in the central nervous system, cerebrovascular disease, stroke, cerebral aneurysm, or movement disorder; (3) Diagnosis of a current psychotic disorder, such as substance-induced psychosis, psychotic disorder due to a medical condition, or MDD with psychotic features at the time of screening; (4) Diagnosis of a current personality disorder that may hinder participation in this research or may have the potential of affecting cognition and the ability to fully participate in the study; (5) Presence of a learning disability as identified through medical history or by the investigator during the assessment process; (6) Involvement in any drug or device clinical trial within the last 6 weeks before the screening visit or involvement in another clinical trial for the duration of this study; and (7) Identification of or the sudden appearance of any condition identified by the investigators to have the potential to hinder the progress and completion of the trial, or be a confounding factor for the outcome assessment.

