### Sample Size Calculation

This study is a pilot study with no standardized data documented on the effect size, which could aid in power and sample size calculations. We will therefore use data that can be generated from the study participants recruited within the existing protocol. This approach is accepted for pilot studies that consist of novel interventions, such as this, and this method has been described by Haynes et al [85] as using “the participants I can get.” In this regard, the study will be limited to a sample size of about 200 (120 from Edmonton and 80 from Halifax), with 100 participants recruited in each of the study arms. Since TRD is characterized by periods of relapses and depressive attacks, we anticipate a certain number of eligible patients to decline to enroll in the study or even drop out before the completion of the study.

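### Per-visit ANCOVA with last observation carried forward as the only named missing-data method can bias the 3- and 6-month PHQ-9 comparison

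*Protocol article*

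**What the plan says.** Data Analysis adopts intention-to-treat and lists repeated-measures analysis among its methods, but describes no repeated-measures model. The comparison it does describe is a one-way ANCOVA of change from baseline to 6 weeks, 3 months and 6 months, with the baseline score as covariate. Missing data are covered by one sentence: "For participants with missing data, the last observation will be imputed before performing sensitivity analyses of covariance to explore the impact". No other method for missing scores is named.

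Other sections bear on this:
- Sample Size Calculation links relapse to attrition, expecting that some patients will decline or "even drop out before the completion of the study". It gives no rate.
- Recruitment Process stops data collection once a participant withdraws.
- Interventions gives both rTMS and the text messages for 6 weeks, so the 3- and 6-month visits come after treatment.
- Background states that "an estimated 80% of patients with TRD relapse within 1 year after remission of their symptoms".
- Strengths of This Study wants the data up to 6 months to show how durable the effect is.

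**The concern.** LOCF is confined to sensitivity analyses, so the main ANCOVAs appear to be unimputed. An ANCOVA at one visit cannot use a participant who has no score there. A patient seen at 6 weeks and 3 months but not at 6 months contributes nothing to the 6-month comparison, although those two scores say much about how that patient was doing. If drop-out depends on those scores and differs by arm, the participants left at 6 months are no longer comparable.

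The fallback has a different weakness. LOCF enters the last score as if it had been measured at 6 months. For a patient who leaves after improving, it assumes that the improvement lasted, and durability is what the follow-up is meant to measure. The messages give one arm daily contact for 6 weeks and then stop, so both unequal drop-out and a changing treatment difference are plausible.

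The Introduction and Discussion say that the effect sizes will feed the power calculation of a full-scale trial. A biased estimate would carry over into that design.

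**Working it through.** **Inputs from the article.** 100 per arm; 1:1 allocation; two-sided 5% level; baseline-adjusted ANCOVA per visit; LOCF in sensitivity analyses only. There is no drop-out rate, PHQ-9 standard deviation or expected effect, so there is no stated figure on this point to reproduce.

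**Inputs assumed.** Drop-out is monotone after the first or second follow-up. Estimates are 6-month differences in PHQ-9 points; negative favours rTMS plus Text4Support.
- Set A: 100 per arm, SD 6, mean PHQ-9 rising from 11 at the first follow-up to 13.5 at 6 months, 2,000 trials.
- Set B: 100 per arm, SD 6, correlation 0.6, 2,000 trials.
- Set C: 1,000 per arm, 60 runs (to separate bias from noise), SD 5, lag-1 correlation 0.6, means 18, 11, 12.5 and 14 at baseline, 6 weeks, 3 and 6 months.

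Three analyses were compared: ANCOVA on observed cases, ANCOVA after LOCF, and a sequential regression using all earlier visits (the analogue of a likelihood-based model).

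**LOCF by hand.** When drop-out is unrelated to scores, the expected LOCF mean in an arm is the sum, over visits, of the share last seen at that visit times the arm's mean there.

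*Effect fading −3, −1.5, 0; 30% random drop-out in each arm.* With the same drop-out probability h at each step, (1 − h)² = 0.70, so h = 0.163. The share last seen at the first follow-up is 0.163, and at the second 0.837 × 0.163 = 0.137. The LOCF difference is 0.163 × (−3) + 0.137 × (−1.5) + 0.70 × 0 = −0.69, although the true value is 0. If all 30% left after the first follow-up it would be 0.30 × (−3) = −0.90. If all left after the second it would be 0.30 × (−1.5) = −0.45.

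*No effect at any visit; random drop-out with step probability 0.10 in control and 0.20 in intervention (Set C means).* Control shifts from 14 by 0.10 × (−3) + 0.09 × (−1.5) = −0.435. Intervention shifts by 0.20 × (−3) + 0.16 × (−1.5) = −0.84. The difference is −0.405, produced only by unequal drop-out in a worsening illness.

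**Simulation results.**

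| Scenario (control / intervention drop-out) | True | Observed-case | LOCF | All-visits |
|---|---|---|---|---|
| C: constant −2, random, 28% / 27% | −2 | −2.01 | −2.01 | −2.00 |
| A: fading −3 to 0, random, 30% / 30% | 0 | −0.03 | −0.72 | −0.02 |
| B: same | 0 | 0.02 | −0.69 | 0.02 |
| C: fading −2 to 0, random, 28% / 28% | 0 | −0.03 | −0.46 | −0.03 |
| C: growing 0 to −2, random, 28% / 28% | −2 | −2.00 | −1.54 | −1.98 |
| C: no effect, random, 19% / 36% | 0 | −0.01 | −0.39 | 0.00 |
| C: no effect, worse scores leave, 24% / 40% | 0 | −0.32 | −0.22 | −0.01 |
| A: constant −2, worse scores leave, 40% vs 20% | −2 | −1.21 | −1.69 | −2.00 |
| B: same type, 44% / 20% | −2 | −1.48 | −1.86 | −2.01 |
| C: same type, 40% / 18% | −2 | −1.60 | −1.77 | −2.02 |

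In the fading scenario, LOCF rejects the null in 13.2% (A) and 13.3% (B) of trials, against a nominal 5%. In the score-driven scenario, power falls from 67.6% with full data to 22.1% in observed cases (A), and from 66% to 33% (B).

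**Reading.** The fading scenario faults only LOCF; the main analysis is unbiased there. Bias in the main analysis needs drop-out that depends on post-baseline scores and differs by arm. The all-visits method does well partly by construction, because all these data were generated as missing at random given the observed scores.

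**The case against.** The strongest reply is that the article never says the main ANCOVAs exclude anyone. It commits to intention-to-treat and mentions repeated measures, and an article may leave the model to a fuller plan. That stands to this extent: observed-case analysis is an inference. It is a strong one, because the described comparison is a per-visit ANCOVA and imputation is reserved for sensitivity analyses. LOCF itself is stated text, not a detail left open.

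A second reply is that nothing shows bias will occur. That also stands: with equal random drop-out and a constant difference there is none. Data Collection and Follow-Up Assessment plans two reminders and then personal contact. These reduce missing surveys but do not settle how the remaining gaps are analysed.

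Some stronger readings are tempting but not supported:
- A reader might take the restriction "for participants who complete the instruments at both time points" as proof that the arm comparison is completers-only. It belongs to the paired t test of baseline against 6 weeks and has no part in the 3- and 6-month comparison of arms.
- A reader might infer that the criterion "Identification of or the sudden appearance of any condition identified by the investigators to have the potential to hinder the progress" allows removal after randomisation. It stands among the eligibility criteria and can mean a condition arising before randomisation. Nothing says such participants leave the analysis, and intention-to-treat points the other way.
- The 80% relapse figure concerns patients who have remitted, over one year. It makes LOCF implausible for those who leave after improving but does not describe all who drop out. Someone with no follow-up score would have baseline carried forward, which is a different assumption.

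**Conclusion.** The point holds as a risk of bias and should be corrected, but it does not show that this trial's result will be biased. The plan pairs a per-visit ANCOVA, by inference on observed cases, with LOCF as its only stated check, and neither makes sound use of the intermediate PHQ-9 scores.

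Under the assumed inputs, the error at 6 months runs from nothing to about 0.7 points for LOCF (an early 3-point benefit that fades, 30% random drop-out). For the main analysis it is about 0.4 to 0.8 points of a true 2 (about 40% versus 20% score-driven drop-out). These figures show the mechanism; the article gives no drop-out rate or mechanism from which to predict the actual size or sign.

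A reader might conclude that the two planned analyses err in opposite directions. That appeared only under a special assumption, with worse patients leaving control and better patients leaving intervention (33% each, true value 0: observed-case +1.13, LOCF −1.22). In the other score-driven scenarios tabulated, both erred the same way.

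**What to change.** Make the main analysis one likelihood-based mixed model for repeated measures on all observed PHQ-9 scores of all randomised participants. Include arm, visit, arm-by-visit and baseline PHQ-9, and read the arm contrast at each visit. State that it assumes data are missing at random given the observed scores. This would also give content to the repeated-measures analysis that Data Analysis names but does not describe.

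Replace LOCF with a sensitivity analysis for data missing not at random, such as multiple imputation with a range of delta shifts for participants who drop out.

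The cost is a change of wording and slightly more programming, chiefly for the delta-adjusted imputation. The mixed model runs in the named software on data already planned, with no extra visits. The Results section says recruitment has not begun, so the change can be made before any data are seen.

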### Randomization and Blinding

A simple randomization technique will be employed using a single sequence of random assignments. The simple randomization will be performed using a computer-generated Excel sheet (Microsoft Corp). To ensure balance (1:1), the randomization will be stratified by using permuted blocks. The codes generated will then be transmitted via text message by an independent statistician directly to a blinded researcher’s password-protected phone line with a secure online backup. This process will occur for enrollment as each participant signs the consent form.

Since blinding of participants in this study is impossible, their treatment allocation will be made known to them right after the randomization process. Primary outcome assessors will not be granted access to the database that contains the randomization codes, and they will not be involved with all discussions concerning the study participants and may be blinded to the treatment arm allocations. The data that would be generated from the study will undergo a blind review for the reason of finishing the planned analysis.

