### Outcome Measures

The primary outcome measure for the study will be changes in the mean score of the Patient Health Questionnaire-9 (PHQ-9) [86] from baseline to the specified time points for the intervention and control groups. With 9 items, the PHQ-9 is half the length of many other depression measures, has comparable sensitivity and specificity, and is made up of the actual 9 criteria upon which the diagnosis of depressive disorders is based according to the Diagnostic and Statistical Manual of Mental Disorders, Fourth Edition. This instrument has the potential to establish major depressive disorder diagnosis, as well as grade the severity of depressive symptoms [86]. The PHQ-9 has good psychometric qualities with high internal consistency, and Cronbach α values of .86 and .89 were obtained in a study that included 2 separate patient populations [87]. The secondary outcome measure will include the 7-item Generalized Anxiety Disorders Scale (GAD-7) [88]. The GAD-7 score is calculated by assigning scores of 0, 1, 2, and 3 to response categories. The GAD-7 total score for the 7 items ranges from 0 to 21, with a score of 0-4 indicating minimal anxiety, 5-9 indicating mild anxiety, 10-14 indicating moderate anxiety, and 15-21 indicating severe anxiety. The GAD-7 has excellent internal consistency (Cronbach α=.92) and test-retest reliability (intraclass correlation=0.83) [88]. The screen version of the Columbia-Suicide Severity Rating Scale (CSSRS) [89] will be included to measure the suicidal ideation of participants. The CSSRS is made up of 6 questions. Users are required to respond “Yes” or “No” to whether they have thought about suicide, have acted or plan to act, or have attempted or plan to attempt suicide. Each of the 6 questions evaluates a different component of the respondent’s suicidal ideation severity and behavior. This measuring tool is scored as low, moderate, or high risk, depending on positive answers (Yes) to the various questions. If a respondent answers positively (Yes) to question 2, the respondent is instructed to respond to questions 3-5. If a respondent answers “No” to question 2, the respondent may skip to question 6. Responding “Yes” to any of the 6 items may imply a need for referral to a mental health care professional, but responding “Yes” to question 4, 5, or 6 indicates a high risk. The CSSRS intensity of ideation subscale has good internal consistency, with Cronbach α values ranging between .73 and .93 [89]. Additionally, the World Health Organization-Five Well-Being Index (WHO-5) [90] will be employed to measure the quality of life of participants. The WHO-5 is a psychometrically robust questionnaire with high internal consistency (Cronbach α=.923) [91]. The WHO-5 is a short questionnaire made up of 5 simple and noninvasive questions, which assess the subjective well-being of respondents. A respondent is asked to rate how well each of the 5 statements applies to them within the last 14 days. Each of the 5 items is scored from 5 (all of the time) to 0 (none of the time). The raw score therefore theoretically ranges from 0 (absence of well-being) to 25 (maximal well-being). To translate the scores to percentages (from 0 [absent] to 100 [maximal]) as required by scales measuring health-related quality of life, the raw score is multiplied 4. The outcome measures and time points for the study are demonstrated in Table 2.

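### The follow-up between-arm tests of PHQ-9, GAD-7, CSSRS and WHO-5 categories leave out the baseline value already collected, an avoidable loss of efficiency in the secondary comparisons

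*Protocol article*

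**What the plan says.** All references are to the protocol article.

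- **Data Analysis, categorical comparisons.** "The chi-square test or Fisher exact test will be employed to compare the prevalence of depression symptoms using the PHQ-9". The sentence goes on to anxiety on the GAD-7, suicidal ideation on the CSSRS and quality of life on the WHO-5, compared between the two arms at all time points. No adjustment is mentioned.
- **Data Analysis, score comparisons.** Scale scores at 6 weeks, 3 months and 6 months are named as dependent variables, and the next sentence reads "Baseline scores of the respective scales will be used as covariates in the analyses". Effectiveness is then compared by ANCOVA of mean change for all measures.
- **Data Analysis, significance.** "The 2-tailed α-level criterion for statistical significance will be set at" P≤.05. The categorical tests are neither exempted nor labelled descriptive.
- **Table 2.** All four scales are collected at baseline and at three follow-up visits.
- **Outcome Measures.** The primary outcome is mean PHQ-9 change. The CSSRS screen is graded as low, moderate or high risk.
- **Sample Size Calculation.** "This study is a pilot study with no standardized data documented on the effect size". The target is about 200, "with 100 participants recruited in each of the study arms".

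**The concern.** Each follow-up category has a baseline value from the same participant on the same scale, usually among the best predictors of follow-up status. A chi-square or Fisher test cannot use it. A participant who was already at high suicide risk before treatment counts the same as one who became high risk, and a chance difference between the arms at baseline passes straight into the follow-up prevalence comparison.

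The cost is power in the categorical comparisons. The Hypothesis section expects superiority on every outcome measure, and these tests share the P≤.05 criterion, so a null or positive prevalence result is likely to be read as evidence about efficacy. The loss matters most for the CSSRS. Its described scoring is a three-level risk category, for which a categorical test is the natural choice, whereas the other three scales have numeric scores that suit the planned ANCOVA.

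**Working it through.** **Inputs from the article.** 100 per arm (Sample Size Calculation), 1:1 allocation (Randomization and Blinding), two-sided 0.05 (Data Analysis). There is no power figure, effect size, SD, prevalence or dropout rate, so the plan has no calculation to reproduce.

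**Assumptions, not in the article.** Baseline and follow-up are bivariate normal with correlation r = 0.3, 0.5 or 0.7. The add-on arm is shifted by 0.4 SD, and follow-up is cut to give 60% prevalence in the control arm.

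**Step 1: prevalence in the add-on arm.** Φ(0.253 − 0.4) = Φ(−0.147) ≈ 0.442, so the comparison is 60% v 44%, a difference of 0.158.

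**Step 2: unadjusted power by formula.** The pooled SE is √(2 × 0.521 × 0.479/100) = 0.0706. The unpooled SE is √((0.240 + 0.247)/100) = 0.0698. Power = Φ((0.158 − 1.96 × 0.0706)/0.0698) ≈ Φ(0.28) ≈ 0.61.

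**Step 3: simulated power.** Each cell gives the uncorrected chi-square test, then logistic regression on arm and baseline.

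| Setting | r = 0.3 | r = 0.5 | r = 0.7 |
|---|---|---|---|
| 60% v 44%, 100 per arm, 4000 replicates | .634 / .640 | .631 / .692 | .643 / .786 |
| Same setting, repeated | .64 / .65 | .64 / .69 | .63 / .79 |
| 50% v 34%, 100 per arm, 2000 replicates | .598 / .610 | .617 / .666 | .618 / .764 |
| 70% v 55%, 100 per arm, 2000 replicates | .583 / .600 | .594 / .668 | .593 / .761 |
| 60% v 44%, 80 per arm, 4000 replicates | .516 / .548 | .519 / .596 | .508 / .682 |

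At 60% v 44% and 100 per arm, the gains are about 1, 5-6 and 14-16 points. The other two cut-points give about 1-2, 5-7 and 15-17. With 80 per arm analysed, the gains are about 3, 8 and 17.

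**Step 4: cross-check through the variance.** In the 60% v 44% setting, adjustment cut the variance of the risk difference by about 5-7%, 15-17% and 31%. The unadjusted ratio of difference to SE is 0.158/0.0698 ≈ 2.27, with approximate power Φ(2.27 − 1.96) ≈ 0.62. Dividing 2.27 by √0.94, √0.84 and √0.69 gives 2.34, 2.48 and 2.73, hence power of about 0.65, 0.70 and 0.78. The size and pattern agree with Step 3.

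**Step 5: validity.** With no true effect, rejection was about 4-6% for both tests. Given a two-standard-error baseline imbalance (2 × √(2/100) = 0.28 SD), the unadjusted rate rose to about 7%, 10% and 15%. An imbalance that large occurs in roughly 5% of trials, so these rates are conditional and are not the overall error rate.

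**Step 6: against the planned ANCOVA.** In the 50% v 34% setting, ANCOVA on the score had power of .839, .896 and .976. At r = 0.5, cutting the score into a category costs about 23 points (.896 v .666), and leaving baseline out of the categorical test costs about 5 more (.666 v .617).

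**The case against.** Several objections stand and set the limits of the point.

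- **A reader might infer that the plan contradicts its own covariate rule.** The text does not support that. The sentence on baseline covariates directly follows one that defines the dependent variables as scores, and the ANCOVA complies with it. The prevalence tests sit in a separate paragraph and cover all time points, which on its face includes baseline, where no baseline adjustment could apply. At most the wording is loose.
- **A reader might infer that the trial's main analysis loses power.** It does not. The primary outcome is mean PHQ-9 change, and the ANCOVA is planned for all measures. The article makes no power claim for its convenience sample.
- **A reader might infer bias.** Randomisation makes the unadjusted test valid, as Step 5 shows.
- **A reader might infer harm to the effect sizes meant for the full-scale trial.** Data Analysis assigns confidence intervals and effect sizes to the continuous measures, and only frequencies and percentages to categorical ones. The planned effect sizes therefore come from the score analyses.
- **A reader might infer that the CSSRS has no baseline-adjusted analysis at all.** Data Analysis also lists the CSSRS among the measures compared on mean scores. Whether a mean suits the described grading is a separate question.

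The gains also rest wholly on assumed inputs, and most of the power gap to the ANCOVA comes from categorising, which this change does not undo. It can also be said that a model needs cut-offs and that Outcome Measures gives none for the PHQ-9 or WHO-5. That is true, but the planned chi-square tests need the same cut-offs.

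**Conclusion.** The point holds as one of efficiency in the secondary categorical comparisons. The named tests set aside a baseline value that every participant provides, and a standard model would use it. The gain is negligible at a correlation of 0.3, modest at 0.5 and substantial at 0.7: about 1, 5-6 and 14-16 points of power at 100 per arm. This assumes 60% v 44% prevalence, a normal latent scale and no dropout. The case is strongest for the CSSRS because its described scoring is categorical, but the simulations used two-level outcomes, so they do not measure the gain for a three-level grade.

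The primary PHQ-9 analysis, the validity of the tests and the planned effect-size estimates are not in question.

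**What to change.** In Data Analysis, for the 6-week, 3-month and 6-month between-arm comparisons only:

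- Replace the chi-square or Fisher test with logistic regression on arm and the baseline value of the same scale: the baseline PHQ-9, GAD-7 or WHO-5 score, or the baseline CSSRS level. Use ordinal logistic regression for the CSSRS risk level and for any other outcome kept in more than two ordered bands.
- Report the marginal (standardised) risk difference with 95% CI for binary outcomes, so that the target stays the difference in prevalence between arms. For ordinal outcomes, report the common odds ratio with 95% CI.
- Keep raw counts and percentages as description.
- Use Fisher's exact test only where cells are too sparse to fit the model.

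This takes a few sentences of protocol or SAP text and no new data. The cut-offs must be written down, but the present tests need them too. The small downside is a model-based estimate in place of a simple table test, with a common-odds assumption for the ordinal outcomes. The standardised risk difference may need a short extra programming step.

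### The CSSRS screen yields only a risk category, yet its undefined mean score enters the ANCOVA and paired t test; the suitable categorical test is planned, but its categories are unstated and it is not baseline-adjusted

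*Protocol article*

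**What the plan says.** Scoring (Protocol article, Outcome Measures): "This measuring tool is scored as low, moderate, or high risk, depending on positive answers (Yes) to the various questions". Questions 3 to 5 follow only a Yes to question 2; otherwise "the respondent may skip to question 6". The only level tied to particular items is the top one: a Yes to "question 4, 5, or 6 indicates a high risk". No numeric total is given, whereas the same section gives numeric ranges for the GAD-7 (0 to 21) and the WHO-5 (0 to 25, multiplied by 4).

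Analysis (Protocol article, Data Analysis), three statements that reach the CSSRS:

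- The effectiveness comparison is a one-way ANCOVA "comparing changes in the mean scores from baseline to 6 weeks, and 3 and 6 months for all measures will be employed", with the baseline score of each scale as covariate.
- A paired t test, in participants who completed the instrument both times, will "examine the changes in the mean scores of the PHQ-9, GAD-7, CSSRS, and WHO-5 at baseline and 6 weeks".
- "The chi-square test or Fisher exact test will be employed" to compare, among other things, "suicidal ideations using the CSSRS, and quality of life using the WHO-5 between the 2 intervention groups at all time points".

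The section also assigns frequencies and percentages to categorical variables and means to continuous ones. Before the ANCOVA, "Preliminary checks will be conducted to ensure there is no violation of the assumption of normality", among other assumptions.

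**The concern.** Two stated parts of the article do not fit together. One makes the CSSRS result an ordered category; the other takes its mean, the change in that mean, and a baseline mean-type covariate. To carry out the ANCOVA and the paired t test, the analyst would have to invent a number, either by coding the categories or by counting Yes answers. Neither is a defined outcome, and the choice can alter the result.

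The CSSRS is a named secondary outcome, the hypothesis claims superiority on all outcome measures, and the trial is meant to supply effect sizes for a full-scale trial. An effect size built on an undefined score cannot serve that purpose. The high-risk share, which matters most clinically, is also not what a mean of codes tracks.

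**Working it through.** The article has no CSSRS figure or power calculation to reproduce. The inputs it gives are the scoring rule, the three analyses above and 100 participants per arm. The risk distributions and the codes 1/2/3 below are assumptions.

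**1. A count of Yes answers contradicts the stated risk rule.**

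| Answers | Count of Yes | Risk under the article's rule |
|---|---|---|
| Yes to question 6 only | 1 | high |
| Yes to questions 1, 2 and 3 only | 3 | not high |

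Both patterns are possible under the skip rule. The participant with the lower count carries the higher risk.

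**2. A mean of category codes can stay still while high risk halves.** Mean = 1 × P(low) + 2 × P(moderate) + 3 × P(high).

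- 60/20/20%: 0.60 + 0.40 + 0.60 = 1.60
- 50/40/10%: 0.50 + 0.80 + 0.30 = 1.60

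The difference in means is zero, although high risk is 20% against 10%.

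**3. This depends on the pattern.** Simulated power, 20,000 trials per row, 100 per arm, two-sided 0.05. The two-sample t test on the codes stands in for the ANCOVA without baseline adjustment.

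| Control vs treated (low/moderate/high, %) | Means | t test | 2×2 chi-square, high vs not | 2×3 chi-square |
|---|---|---|---|---|
| 60/20/20 vs 50/40/10 | 1.60, 1.60 | 0.05 | 0.52 | 0.86 |
| 60/20/20 vs 60/30/10 | 1.60, 1.50 | 0.15 | 0.52 | 0.54 |
| 60/20/20 vs 70/20/10 | 1.60, 1.40 | 0.48 | 0.51 | 0.43 |
| 30/30/40 vs 10/70/20 | 2.10, 2.10 | 0.05 | 0.88 | 1.00 |
| 30/30/40 vs 50/30/20 | 2.10, 1.70 | 0.93 | 0.88 | 0.89 |

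The mean fails when the movement is from high to moderate or is offset by movement from low to moderate. When the net movement is from high to low, it does about as well as the high-risk test, or better.

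**4. Which replacement sees the change.** Take the first row as exact counts in 100 per arm: 60, 20, 20 against 50, 40, 10.

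- High vs not: chi-square = 200 × (20 × 90 − 80 × 10)² / (30 × 170 × 100 × 100) = 3.92, p = 0.048.
- Three levels, expected 55, 30, 15 in each arm: chi-square = 2 × (25/55 + 100/30 + 25/15) = 10.91 on 2 df, p = 0.004.
- Proportional odds, unadjusted: odds ratio for higher risk 1.16 (95% CI 0.68 to 1.99), p = 0.58.

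The proportional-odds model fails because the two cuts point in opposite directions. For moderate or high, the odds ratio is (50/50)/(40/60) = 1.5. For high, it is (10/90)/(20/80) = 0.44. An ordinal model as the lead analysis would therefore repeat the weakness of the mean.

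**5. What the right test can do at this sample size.** Normal-approximation power to detect a halving of the high-risk share, 100 per arm:

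| High risk, control to treated | Power | n per arm for 80% power |
|---|---|---|
| 10% to 5% | 0.27 | 435 |
| 20% to 10% | 0.51 | 199 |
| 30% to 15% | 0.72 | 121 |
| 40% to 20% | 0.88 | 82 |

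At 10 to 20%, much of the difficulty comes from the sample size, whichever test is used.

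**The case against.** The strongest reply is that the plan already contains a suitable CSSRS analysis. The chi-square or Fisher test compares the arms at all time points, and in the cancelling example the three-level version has power 0.86. A reader might infer that the plan as a whole would miss a halving of high-risk participants; the article does not support that. What remains is that the test's categories are unstated (any Yes, three levels or high risk) and that it does not use baseline risk. Lack of adjustment does not make it invalid in a randomised trial; adjustment may add precision and matches the plan's own intention to use baseline scores as covariates.

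The equal-mean example was also chosen to cancel, and its codes and distributions are not in the article. This stands: the example shows that masking is possible, not that it is likely.

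A reader might go further and say that the suicidality result would have no clinical meaning, or that the CSSRS is bound to fail the assumption checks. Neither is shown. The categorical comparison is interpretable, and the article gives no CSSRS distribution. If the checks did fail, they would have done their job, and the fallback could sit in a fuller document.

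Finally, coding conventions such as how skipped items count are often left out of an article. That is fair, and their absence is not the point. The point is that the article states both a categorical score and a mean-score analysis of it.

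**Conclusion.** The mismatch holds as a wording and analysis error on one secondary outcome in a pilot trial. The CSSRS screen is given a risk level and no number, and two of the three analyses that include it need a number. This rests on the article's text alone.

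The size of the harm is conditional. Under assumed codes and distributions, a mean-score test of a true halving of high risk has power from 0.05 to 0.93 depending on where participants move, against 0.51 to 0.88 for a high-versus-not comparison in the same scenarios. The mean is therefore unreliable for this purpose, not uniformly blind. The paired t test shares the undefined score but is a within-participant analysis of completers, so it does not bear on the comparison between arms.

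**What to change.** - Remove the CSSRS from the ANCOVA and from the paired t test.
- Make the between-arm comparison of high risk (Yes to question 4, 5 or 6, as the article already defines it) at each follow-up the main CSSRS analysis. Use logistic regression adjusted for baseline risk level, with exact methods if counts are small, and report odds ratios and risk differences with 95% CIs.
- Keep the planned chi-square or Fisher test as support, and state that it uses the three risk levels.
- Use a proportional-odds model only as a further analysis, and only if proportionality holds.
- For within-participant change from baseline to 6 weeks, use McNemar's test on high risk.

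The cost is a change of analysis wording. The baseline and follow-up CSSRS are already collected, so no new data are needed. The small downside is that the CSSRS is no longer reported on the mean-difference scale of the other measures. The change does not cure the limited power at low high-risk shares, so the intervals should be read accordingly.
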